# Effects of proximal priority and distal priority robotic priming techniques with impairment-oriented training of upper limb functions in patients with chronic stroke: study protocol for a single-blind, randomized controlled trial

**DOI:** 10.1186/s13063-021-05561-6

**Published:** 2021-09-08

**Keywords:** Stroke, Upper extremity rehabilitation, Proximal priority, Distal priority, Robotic therapy, Bilateral motor priming, Impairment-oriented training, Randomized controlled trial

## Abstract

**Background:**

The sequence of establishing a proximal stability or function before facilitation of the distal body part has long been recognized in stroke rehabilitation practice but lacks scientific evidence. This study plans to examine the effects of proximal priority robotic priming and impairment-oriented training (PRI) and distal priority robotic priming and impairment-oriented training (DRI).

**Methods:**

This single-blind, randomized, comparative efficacy study will involve 40 participants with chronic stroke. Participants will be randomized into the PRI or DRI groups and receive 18 intervention sessions (90 min/day, 3 days/weeks for 6 weeks). The Fugl-Meyer Assessment Upper Extremity subscale, Medical Research Council Scale, Revised Nottingham Sensory Assessment, and Wolf Motor Function Test will be administered at baseline, after treatment, and at the 3-month follow-up. Two-way repeated-measures analysis of variance and the chi-square automatic interaction detector method will be used to examine the comparative efficacy and predictors of outcome, respectively, after PRI and DRI.

**Discussion:**

Through manipulating the sequence of applying wrist and forearm robots in therapy, this study will attempt to examine empirically the priming effect of proximal or distal priority robotic therapy in upper extremity impairment-oriented training for people with stroke. The findings will provide directions for further studies and empirical implications for clinical practice in upper extremity rehabilitation after stroke.

**Trial Registration:**

ClinicalTrials.gov NCT04446273. Registered on June 23, 2020.

**Supplementary Information:**

The online version contains supplementary material available at 10.1186/s13063-021-05561-6.

## Strengths and limitations of this study

This study will examine the effects of proximal (i.e., forearm first) and distal (i.e., wrist first) priority robotic therapy combined with impairment-oriented training in stroke rehabilitation.This study will investigate the effects of bilateral robotic priming before impairment-oriented training in people with chronic stroke.Predictors of treatment outcome will be examined with the chi-square automatic interaction detector method.Limitations of this study may include the limited size of the study sample.

## Background

Stroke is a leading cause of death [1] and lost productivity worldwide as measured by disability-adjusted life years [2]. Upper extremity (UE) sensorimotor impairments after stroke, such as weakness, abnormal muscle tone or motor synergies, pain, and hypersensitivity or hyposensitivity, are prevalent and persistent [3] and may further affect activities of daily living [4] and quality of life after stroke [5]. Robot training (RT) is emerging as a novel approach to support therapists in their efforts to provide high-intensity, repetitive, and task-specific interventions. Systematic reviews indicate that RT leads to improvement in UE motor impairment and strength in stroke patients but to less improvement in UE functional use and activities of daily living [6].

### Movement-based robotic priming

Motor priming can be defined as a change in motor performance on the basis of previous stimuli and is an emerging strategy to facilitate motor relearning in neurorehabilitation [7]. Bilateral motor priming involves bimanual, repetitive, and mirror-symmetric movement training before other functional training movements are implemented [7] and may promote normalization of transcallosal inhibition and greater balance in excitability between the hemispheres after stroke for improved functional recovery [8]. Therefore, bilateral symmetrical movements in bilateral motor priming are used as a neuromodulation technique. As an adjuvant intervention, bilateral RT may be combined with different types of functional rehabilitation therapies and may yield differential benefits.

### Bilateral robotic priming before impairment-oriented training

Impairment-oriented training (IOT) is an approach developed to restore body functions after stroke, including remediation of motor impairments, rather than functional performance [9]. Sensorimotor deficits (e.g., single joint movements or quality of motor performance) should be treated specifically according to their individual characteristics. Arm BASIS training and Arm Ability training are two programs of IOT that have been developed for treating different severity levels of UE impairments after stroke. Empirical studies have confirmed the effects of these two programs of IOT on motor recovery, restoration of movement and muscle function, and enhanced quality of motor control [10, 11].

A previous pilot study reported that bilateral robotic priming before IOT was beneficial on UE motor function and muscle power [12]. The protocol [12] included 60 min of RT with two types of movement patterns, consisting of forearm pronation-supination and wrist flexion-extension and abduction-adduction, delivered by the InMotion 3.0 robot [13].

The Rood approach for the treatment of patients with stroke is one of the neurophysiological approaches for the facilitation and inhibition of movement [14]. One basic premise of the Rood approach is the movement of the distal body part in a finely coordinated pattern based on the stability of the proximal body part [15]. However, the Rood approach has been criticized for insufficient empirical evidence. In addition, how the two movement patterns (i.e., forearm pronation-supination and wrist flexion-extension and abduction-adduction) of RT were sequenced in the previous study was not clear [12], and the sample size of the bilateral robotic priming and IOT group was very small (*n* = 10).

This study is therefore designed to extend the previous study [12] by examining the effect of proximal (i.e., forearm first and wrist second) priority robotic priming and impairment-oriented training (PRI) and distal (i.e., wrist first and forearm second) priority robotic priming and impairment-oriented training (DRI) with a larger sample size (i.e., *n* = 20 in each group). We hypothesize that the PRI and DRI groups will both improve significantly on normalized muscle tone, sensorimotor impairment, upper limb function, self-efficacy, and quality of life from preintervention to postintervention and that the improvement will be maintained at the follow-up assessment. In addition, this study will compare the relative effects between PRI and DRI. We hypothesize that the PRI group will achieve better proximal UE motor ability and that the DRI group will achieve better distal UE motor ability.

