## Methods and design

### Participants

The inclusion criteria are age between 20 and 75 years, more than 3 months after the onset of a first unilateral ischemic or hemorrhagic stroke, moderate to severe UE motor impairment (total UE score of the Fugl-Meyer Assessment [UEFMA] score between 18 and 56), no severe spasticity in any joints of the affected arm (modified Ashworth Scale score <3 in any of the affected shoulder, elbow, wrist, and fingers), able to follow instructions (Mini-Mental State Examination total score >24), no UE fractures in the past 3 months, and not simultaneously participating in other medication or rehabilitation studies. The exclusion criteria are other neurologic (i.e., epilepsy), neuromuscular, or orthopedic disease, or severe health or physical conditions that might impede participation in this study.

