### Intervention

The PRI and DRI groups will receive an equal amount of treatment time, comprising 1.5 h per day, 3 days per week, for 6 weeks. All other routine interventions, such as physical therapy or medication, will continue as usual throughout the study period, except for the administration of botulinum toxin.

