### Statistical analyses

The Student *t* test and *χ*^2^ will be used to analyze differences in baseline characteristics and outcome measures between the two groups. Two-way repeated-measures of analysis of variance will be used to determine the intervention effects. The within-subject factor is time (i.e., pretest, posttest, and follow-up assessment), and the between-subject factor is group (i.e., PRI and DRI). A post hoc Tukey test will be used when a group × time interaction or a main effect is observed. An *α* level of .05 is set for all statistical comparisons. Partial eta squared (*η*^2^) will also be estimated to determine the group difference for each outcome measure. Predictors of PRI and DRI outcomes will be estimated with the chi-square automatic interaction detector (CHAID) method. Data analyses will be performed using SPSS Statistics 18.0 software (IBM Corp, Armonk, NY, USA).

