In clinical practice, therapists may use techniques targeting several joints of the UE in sequence to promote quality of motor control and functional use of the UE in daily activities. However, no studies to date have investigated the comparative effects of different sequences of training UE joints. Therefore, this study will attempt to extend the previous study [12] by comparing the two combined interventions (i.e., PRI and DRI). Results of this study may provide critical and empirical information about the effects of the training sequence of proximal priority (e.g., forearm first) and distal priority (e.g., wrist first) robotic priming before IOT on motor control and sensorimotor function of UE.

The limited research that is available regarding the effects of bilateral robotic priming combined with IOT provides no information about the responders who are more likely to benefit from this hybrid intervention. Therefore, another goal of this study will be to identify predictors of changes in outcomes after the interventions using the CHAID method. CHAID analysis builds a predictive model to help determine how predicting variables best merge to explain the outcomes in PRI and DRI. CHAID is based on the χ^2^ test to analyze structural linkages between variables and can potentially provide a mechanism for investigating the interaction between demographic and clinical features of patients and outcome measures [20].

Limitations of the design and implementation of this study must also be considered. This is a comparative efficacy study examining two parallel hybrid therapies (i.e., PRI and DRI) and, therefore, does not include a passive control or a conventional rehabilitation group. However, lack of an IOT-only group may limit this study from an estimation of the addictive priming effect of bilateral RT. The sample size of each group (*n* = 20) is small, which reflects the restriction of recruiting large samples of patients with stroke for efficacy studies.

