Hemiparesis of the contralateral UE has a significant negative impact on activity participation and social involvement after stroke. There are imperative needs to identify an effective rehabilitation program and characteristics of responders to promote sensorimotor recovery and functional use of the affected UE. The results of this study will provide evidence for the bilateral robotic priming hybrid with IOT on sensorimotor function of UE after stroke. This study will validate the differential effects of sequences in involving joints in UE rehabilitation (i.e., proximal or distal joint first). Implications of these findings will inform the clinical practice of UE rehabilitation in chronic stroke.

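### The first hypothesis and the promised evidence for the combined therapy rest on uncontrolled within-arm change; the design identifies only the PRI-DRI difference.

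*Protocol article*

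**What the plan says.** In the Background, under Bilateral robotic priming before impairment-oriented training, the protocol states two hypotheses. The first concerns change within each arm: the groups "will both improve significantly on normalized muscle tone, sensorimotor impairment, upper limb function, self-efficacy, and quality of life from preintervention to postintervention", with the gain kept at follow-up. The second concerns the difference between arms: "We hypothesize that the PRI group will achieve better proximal UE motor ability and that the DRI group will achieve better distal UE motor ability".

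The PRI group and DRI group sections give each arm 45 minutes of robot training followed by 45 minutes of IOT. The intended difference is whether the forearm or the wrist mode of the robot comes first.

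Statistical analyses plans a two-way repeated-measures ANOVA (time by group) as the means of determining intervention effects. Post hoc tests follow an interaction or any main effect, and "An *α* level of .05 is set for all statistical comparisons".

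The Discussion makes three statements that bear on this:

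- Its first paragraph says that the study will examine the immediate and follow-up effects of combining bilateral robot training with IOT.
- Its limitations paragraph says that the trial has neither a passive control nor a conventional rehabilitation arm, and that "lack of an IOT-only group may limit this study from an estimation of the addictive priming effect of bilateral RT".
- Its closing paragraph says: "The results of this study will provide evidence for the bilateral robotic priming hybrid with IOT on sensorimotor function of UE after stroke".

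**The concern.** Everyone in the trial receives robot training plus IOT, so no planned comparison sets the combination against anything else. The first hypothesis can be confirmed only by change from baseline, and such change has other possible sources that the protocol itself allows:

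- Routine care (Intervention): "All other routine interventions, such as physical therapy or medication, will continue as usual throughout the study period", apart from botulinum toxin.
- Recovery (Participants): entry is open to patients "more than 3 months after the onset" of stroke.
- Retest effects (Design and procedure): the outcomes are assessed on three occasions.

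A significant time effect with no group-by-time interaction would fit the first hypothesis and could be reported as evidence for the combined therapy, although the same result can arise with no treatment effect. What is at stake is the trial's headline efficacy conclusion. The validity of the randomized comparison is not in question.

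**Working it through.** **What each statement needs, and whether the design supplies it**

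| Statement | Comparison needed | Available? |
|---|---|---|
| Both arms improve because of the therapy (first hypothesis, read causally) | Combination against no or other treatment | No |
| Effects of the combination (Discussion, first paragraph) | Same | No |
| Evidence for the combination (Discussion, closing paragraph) | Same | No |
| PRI better proximally, DRI better distally (second hypothesis) | PRI against DRI | Yes, randomized |

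The ANOVA contains both kinds of test. The time main effect pools the arms and has no comparator. The group-by-time interaction is the randomized contrast.

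**How easily within-arm change becomes significant without a treatment effect**

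The protocol gives no effect size, SD or power figure, so there is no calculation of its own to reproduce. What follows is an illustration.

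Inputs from the protocol: 20 per arm, 40 in total (Background), and α = 0.05 (Statistical analyses). Two-sided testing is assumed, because sidedness is not stated.

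Inputs assumed: zero treatment effect; the same non-treatment change (drift) d in both arms, in baseline SDs; equal SDs before and after; pre-post correlation r = 0.8.

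1. The SD of change is √(2(1 − r)) = √0.4 = 0.632 baseline SD, so the standardized change is dz = d / 0.632.
2. The test is a paired t test with n − 1 degrees of freedom and noncentrality dz·√n. Critical values are 2.093 (n = 20) and 2.023 (n = 40).
3. The chance that both arms improve significantly is the square of the one-arm chance of significant improvement, because the arms are independent.

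| d | dz | Pooled, n = 40 | One arm, n = 20 | Both arms improve |
|---|---|---|---|---|
| 0.1 | 0.158 | 16% | 10% | 0.099² = 1% |
| 0.2 | 0.316 | 50% | 27% | 0.269² = 7% |
| 0.3 | 0.474 | 83% | 52% | 0.521² = 27% |

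With r from 0.7 to 0.9, the pooled figure runs from 36% to 79% at d = 0.2 and from 67% to 99% at d = 0.3.

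**The randomized contrast under the same conditions**

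Drift common to both arms cancels in the difference between their changes. In 20,000 simulated trials at each drift from 0 to 0.8 SD of change, with no treatment effect, the between-arm test rejected in 5.1% to 5.3% of trials.

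The figures are for one outcome and use the pre-post contrast only, not the planned three-level time factor.

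**The case against.** The strongest reply is that the protocol already treats this as a comparison of two active therapies. The Abstract ties the ANOVA to comparative efficacy, partial eta squared is to describe the group difference, and no sentence says that a time main effect will be read as efficacy. A hypothesis about change can also be stated and tested as no more than that; only causal attribution is at fault. This stands in part. The misreading is an inference from the first hypothesis, the stated purpose of the ANOVA, the follow-up of any main effect and the two Discussion statements. But those two statements are attributions to the combined therapy, and nothing in the plan limits them.

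Four stronger readings are tempting, and the protocol does not support them:

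- *That the missing control is concealed.* It is disclosed plainly. What is missing is the consequence: the limitation that is drawn concerns the added effect of priming over IOT, not the attribution of within-arm change to the combination.
- *That the Abstract's reference to a priming effect contradicts the limitations.* There the effect is tied to manipulating the sequence of the robots, which is the randomized contrast. That sentence needs no change.
- *That a false confirmation of the first hypothesis is likely.* The 83% is one pooled test at the largest drift shown. The hypothesis requires both arms to improve, for which the figure is 27% at that drift and lower at smaller ones. Long after stroke, non-treatment change may be small.
- *That the trial needs a control arm.* A two-arm comparison of training order is a legitimate question.

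**Conclusion.** The point holds as a fault of inference. The first hypothesis, the time main effect as a measure of intervention effects, and the two Discussion statements about the combination all go beyond what the design identifies, and they do not fit the trial's own limitations paragraph. This follows from the design and does not depend on any assumed number.

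The size of the risk does depend on assumptions. At r = 0.8 and drift of 0.1 to 0.3 baseline SD, a null therapy gives a significant pooled change in 16% to 83% of trials, and significant improvement in both arms in 1% to 27%. The protocol supplies neither the drift nor the correlation. The PRI-DRI comparison keeps its error rate of about 5%, and the sample size is unaffected.

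**What to change.** - In Statistical analyses, base efficacy conclusions only on the randomized PRI-DRI comparison (group by time).
- Report change within each arm descriptively, as mean change with a 95% confidence interval, and draw no efficacy claim from the time main effect. Mark the first hypothesis as descriptive to match.
- In the first and closing paragraphs of the Discussion, limit the promised conclusions to the comparison of two training orders. In the limitations paragraph, add that without a control arm within-arm improvement cannot be attributed to the combination.

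Nothing changes in sample, visits, treatment or data collection. The cost is a narrower role for the first hypothesis and a less favourable headline claim.

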### Design and procedure

The study will use a single-blind randomized pretest and posttest design. Potential participants will be identified by the therapists or research assistants, and the study procedures, risks, and benefits will be explained. All participants will sign the informed consent before enrolling in this study and be allocated to the PRI or DRI groups based on a computer-generated random-sequence table (Table 1). The second author of this study ([name]) will generate the allocation sequence, enroll participants, and assign participants to interventions. Allocation concealment is ensured, as the computer-generated random codes are not released. The study will recruit 40 patients with stroke from hospital settings. Initial and outcome assessments will be administered by a well-trained and certified occupational therapist who is blinded to the group assignment, study hypotheses, and intervention of the patients. Trial participants, care providers, outcome assessors, and data analysts will be blinded after assignment to interventions. Unblinding is permissible when knowledge of the actual treatment is absolutely essential for further management of the patient.

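### The protocol hypothesizes that gains are maintained at 3 months but plans only tests of difference, none of which can support a no-loss claim

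*Protocol article*

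**What the plan says.** The Background of the protocol article, under the heading on bilateral robotic priming before impairment-oriented training, states the hypothesis for each arm, with quality of life as the last domain listed: "We hypothesize that the PRI and DRI groups will both improve significantly on normalized muscle tone, sensorimotor impairment, upper limb function, self-efficacy, and quality of". The same sentence adds that "the improvement will be maintained at the follow-up assessment". Follow-up is 3 months after treatment ends.

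Under Statistical analyses, "Two-way repeated-measures of analysis of variance will be used to determine the intervention effects", with three visits as the within-subject factor and arm as the between-subject factor. Then "A post hoc Tukey test will be used when a group × time interaction or a main effect is observed", and "An *α* level of .05 is set for all statistical comparisons". Partial eta squared is the only effect measure named, and it is tied to the difference between groups. No definition of *maintained*, no margin and no interval for the change after treatment is given.

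The sample is "20 in each group". No power basis is shown; the Discussion explains the size as a limit on recruitment ("which reflects the restriction of recruiting large samples of patients with stroke for efficacy studies").

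**The concern.** That a gain is maintained can mean two things: some of it is still there at 3 months, or it has not been materially lost. The planned tests can address the first meaning but not the second.

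- **Follow-up versus pretest.** A significant result shows that some improvement remains. It does not show how much of the posttest gain was kept.
- **Posttest versus follow-up.** This is the contrast that bears on loss. A significant fall counts against maintenance, but a non-significant one is not evidence for it. The noisier the data, the easier non-significance is to obtain.

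At stake is a durability statement for both arms on many outcomes, in a trial whose Discussion makes follow-up effects part of its purpose and expects the results to inform practice. If a non-significant fall in 20 patients were reported as a maintained gain, readers could take a partly lost benefit for a lasting one.

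**Working it through.** The protocol gives no power, SD or expected loss, so there is no figure of its own to reproduce. The question is how informative a non-significant fall would be.

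**Inputs from the protocol.** n = 20 per arm, 40 in total; three visits; α = .05, taken as two-sided because sidedness is not stated.

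**Assumptions.** The true posttest-to-follow-up fall is expressed as d, in SDs of the within-patient change, with d = 0.4 and 0.5 as the main cases. No dropout. A d of 0.4 is half of a 0.8 SD gain; 0.5 is half of a 1.0 SD gain.

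**Formula.** Power = 1 − F(c; df, d√n), where F is the noncentral t distribution function and c the critical value. Miss rate = 1 − power. The noncentrality d√n is 0.4 × √20 = 1.79 and 0.5 × √20 = 2.24 for one arm, and 0.4 × √40 = 2.53 and 0.5 × √40 = 3.16 for both arms pooled. For Tukey over three visits, c is the studentized range quantile divided by √2.

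| Comparison | c | Miss rate, d = 0.4 | Miss rate, d = 0.5 |
|---|---|---|---|
| One arm, paired t, df 19 | 2.09 | 1 − 0.397 = 60% | 1 − 0.564 = 44% |
| One arm, Tukey, df 38 | 2.44 | 1 − 0.271 = 73% | 1 − 0.429 = 57% |
| One arm, Tukey, df 76 (error term from both arms) | 2.39 | 1 − 0.280 = 72% | 1 − 0.443 = 56% |
| Both arms pooled, Tukey, df 76 | 2.39 | 1 − 0.557 = 44% | 1 − 0.778 = 22% |

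**Where missing becomes the minority outcome.** Power in one arm reaches 50% at d = 0.46 (paired t) and at 0.53–0.54 (Tukey). It reaches 80% at 0.66 and 0.72–0.74. Pooled Tukey reaches 50% at 0.38 and 80% at 0.51.

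**Larger losses.** Half of a 1.5 SD gain (d = 0.75) is missed by a paired t test in 1 − 0.889 = 11% of trials. Loss of a whole 0.8 SD gain is missed in 1 − 0.924 = 8%.

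**Both arms together.** The hypothesis requires both arms to improve and to maintain. Simulation with equal SD of change for every pair of visits, and Tukey within each arm, gives the chance that an arm shows a significant gain but no significant fall when half the gain is truly lost. That chance is about 60%, 55% and 18% at gains of 0.8, 1.0 and 1.5 SD. The arms are independent, so for both arms it is 0.60² = 36%, 0.55² = 30% and 0.18² = 3%.

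**What an interval would deliver.** The 95% half-width for one arm's mean change is 2.093/√20 = 0.47 SD of the change. If there is truly no loss, the lower limit clears a margin of 0.5 SD with 56% power and a margin of 0.66 SD with 80%. For 80% power at a 0.5 SD margin, 34 patients per arm are needed. These margins are illustrative; the protocol gives none.

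**The case against.** Four points can fairly be made on the other side.

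1. **No faulty rule is stated.** A reader might infer that the protocol will declare maintenance from a non-significant fall. No sentence says so; it gives no criterion at all. An analysis plan that is not shown could define one. This stands, and it limits the point to a mismatch between the stated hypothesis and the stated analysis.

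2. **One reading is served.** If *maintained* means still better than baseline, follow-up versus pretest is a valid test, and imprecise data make success harder, not easier. This also stands, but the contrast cannot show that the improvement was kept.

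3. **Losses would not generally go unnoticed.** A reader might infer that a trial losing half its benefit would usually still support the hypothesis. The figures do not bear that out: for both arms it happens in about 36%, 30% and 3% of trials at gains of 0.8, 1.0 and 1.5 SD. It is a majority outcome only for a single arm with Tukey at gains near 0.8 to 1.0 SD. After a time main effect without interaction, the Tukey step would ordinarily compare visits over all 40 patients, and the lower pooled miss rates then apply. Nor can this be asserted outcome by outcome, since the protocol gives no SD or expected change for any of them.

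4. **The claim is secondary.** It is an uncontrolled within-arm statement, and the protocol already concedes a small sample. This bears on severity. It does not supply the missing analysis.

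**Conclusion.** The point holds in a limited form. The protocol hypothesizes maintained improvement in both arms and plans only difference tests. One of those can show that some gain persists; none can support the conclusion that the gain was not materially lost.

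The weakness of a non-significant fall as evidence depends on its true size. In one arm of 20, falls of 0.4 to 0.5 SD of the change are missed about as often as they are found, or more often. Falls above about 0.54 SD are usually detected even with Tukey. These figures rest on assumed effect sizes, two-sided testing and no dropout.

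Severity is modest. The randomized comparison of the two training sequences is not affected.

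**What to change.** Add to Statistical analyses:

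- For each primary outcome and each arm, report follow-up minus posttest and follow-up minus pretest with 95% confidence intervals, signed so that higher is better (WMFT-Time reversed).
- State that a non-significant posttest-to-follow-up change is not evidence of maintenance.
- Use *maintained* only if the lower confidence limit of follow-up minus posttest excludes a loss larger than a margin that the sponsor fixes and justifies in advance. Otherwise describe the result as gain retained relative to baseline.

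The cost is a few sentences, plus a margin for any primary outcome on which a maintenance claim is wanted; no new data are needed. The downside is that maintenance will be claimed less often. With a half-width of about 0.47 SD of the change, 20 patients per arm have 80% power only at a margin of about 0.66 SD, so for most outcomes the realistic product is the interval itself.
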